#### Data analysis

2.6.4

The quantitative imaging data will then be correlated with chemical and pathological markers of ischemia (Capillary lactate levels, mitochondrial chain respiratory rates, histopathological assessment, and immunohistochemical markers of ischemia) and with postoperative morbidity and mortality, including radiological or clinical AL (recorded and scored using the Clavien-Dindo scale). Based on a receiver operating curve we hope to determine a cut-off value for the prediction of gastric graft malperfusion, based on the Youden index.

### Statistical analysis

2.7

Study data will be collected in an excel data collection sheet, in which descriptive statistics can be provided for all measured parameters. Quantitative data are expressed as mean and/or median with standard deviation, interquartile range, or min-max range. Data will be analyzed using standard statistical software (SPSS version 22 for windows, SPSS Inc, Chicago, IL). An ROC curve for sensitivity and specificity for leakage as binary classifier will be constructed. From this curve, the Youden index will be used to calculate a best-fit cut-off point. Statistical analysis using chi-square test, Fisher exact test, and Mann-Whitney *U* test will be performed whenever needed. A *P* value <0.05 is considered statistically significant.

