### Study objectives and endpoints

2.2

The primary endpoint will be to determine an ICGA-based cutoff point to predict AL and graft necrosis after esophageal reconstructive surgery. This cutoff value will be an ICGA fluorescent intensity time measurement expressed in seconds.

Secondary endpoints are the following:

The evaluation of ICGA as a quantitative perfusion imaging modality during gastric tube reconstruction. First, intensity over time curves will be analyzed in the regions of interest to generate quantitative values for maximal fluorescence intensity (*I*_max_), inflow time (*T*_inflow_), and outflow time (*T*_outflow_). Second, a kinetic modeling analysis of the time-varying ICG concentration images will be performed, based on a tracer kinetic model that was developed to measure tissue blood flow and vascular permeability.The validation of ICGA imaging by comparing the quantitative data:

To continuous perioperative hemodynamic measurements from a Pulse index Continuous Cardiac Output (PiCCO) catheter.To biological markers of hypoxia and ischemia: systemic and capillary lactate levels (measured in systemic and serosal blood samples) and mitochondrial chain respiratory rates (measured on tissue biopsies).And to histopathological ischemic markers of hypoxia and ischemia.Patient outcome in terms of AL and necrosis defined by the Esophagectomy Complications Consensus Group (ECCG) classification and identified by clinical and radiological methods. Based on a receiver operating curve we hope to determine a cut-off value for the prediction of gastric graft malperfusion.Product-related toxicity.Surgery-related endpoints: number of crossover patients: perioperative change of anastomotic site based on ICG findings, perioperative blood loss, and perioperative adverse events.Incidence of minor and major adverse events up to 30 days postoperatively classified by the Clavien-Dindo score and based on the ECCG international consensus for complications associated with esophagectomy.^[25]^Intensive care unit and in hospital stay and finally incidence of stricture up to 1 year postoperatively.

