### Sample size

2.4

For the sample size we focused on the accuracy with which the ICGA quantitative parameters will be able to predict AL. For an alpha = 0.05 and a power of 0.80, a total sample size of 54 patients is required to be able to show a statistically significant difference of the area under the curve in a receiver operating characteristic curve (ROC), provided that a leak rate of 16% is observed. Including a 10% drop out or lost to follow-up, we intent to include 70 patients.

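### The primary endpoint is a Youden cut-off that the analysis produces unconditionally, and nothing ties it to the AUC test on which the study is sized

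*Protocol article*

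**What the plan says.** All references are to the protocol article.

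- **Section 2.2 (endpoints):** "The primary endpoint will be to determine an ICGA-based cutoff point to predict AL and graft necrosis after esophageal reconstructive surgery". The cut-off is to be a time in seconds. No minimum AUC, sensitivity, specificity or Youden index is attached.
- **Section 2.7 (statistical analysis):** an ROC curve for leakage is built, and then "From this curve, the Youden index will be used to calculate a best-fit cut-off point". Section 2.6.4 also names the Youden index, and expresses the cut-off as something the authors hope to obtain.
- **Section 2.4 (sample size):** "For an alpha = 0.05 and a power of 0.80, a total sample size of 54 patients is required", the purpose being "to be able to show a statistically significant difference of the area under the curve in a receiver operating characteristic curve (ROC", and this "provided that a leak rate of 16% is observed". Neither the null AUC nor the alternative AUC is given.
- **Section 2.7, tests:** "Statistical analysis using chi-square test, Fisher exact test, and Mann-Whitney *U* test will be performed whenever needed", and "A *P* value <0.05 is considered statistically significant". No test is assigned to the primary endpoint.

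**The concern.** The study is sized on one question (is the AUC significantly different from a reference value?), while its primary endpoint is another (where is the cut-off?). The Youden rule uses the leak data only to locate the maximum of sensitivity + specificity − 1. It does not ask whether that maximum is larger than chance would give, and almost every empirical ROC curve has some point above the diagonal.

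Followed literally, the primary analysis therefore produces a threshold in seconds for predicting leakage whether or not ICGA time carries information. The discussion in section 3 looks ahead to predicting, and so avoiding, leakage, and a threshold in seconds is easy to adopt in theatre. This differs from optimism in the sensitivity and specificity at the chosen point. Correcting that optimism would still leave open when the cut-off may be called predictive.

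**Working it through.** **Inputs.** From section 2.4: alpha 0.05, power 0.80, leak rate 16%, N = 54, enrolment 70, dropout 10%. Patients evaluable after 10% loss: 70 × 0.90 = 63. Expected leaks: 0.16 × 54 = 8.6, 0.16 × 63 = 10.1, 0.16 × 70 = 11.2. The leak/no-leak splits used are 9/45, 10/53 and 11/59. Assumptions, because the article does not state them: null AUC 0.50, a continuous marker, slower time taken in advance as higher risk, and true AUCs of 0.70 to 0.80 for power.

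**Step 1: the plan's figure of 54.** It cannot be reproduced from the stated inputs, since no AUC is given. The Hanley-McNeil variance shows what it would imply:

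Var(A) = [A(1−A) + (n1−1)(Q1−A²) + (n0−1)(Q2−A²)] / (n1·n0), with Q1 = A/(2−A) and Q2 = 2A²/(1+A).

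With n1 = 8.64 and n0 = 45.36, the standard error is 0.108 at A = 0.50 and 0.096 at A = 0.79. Two-sided power at 0.79 is Φ[(0.29 − 1.96 × 0.108)/0.096] ≈ Φ(0.81) ≈ 0.79. The N needed for 80% power is 122 at AUC 0.70, 77 at 0.75, 56 at 0.79 and 52 at 0.80. So 54 fits a two-sided test with an assumed AUC of about 0.79 to 0.80 (about 0.76 if one-sided). It is a calculation for a test of discrimination, not for locating a cut-off.

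**Step 2: how often the Youden step gives J > 0 with no association.** All orderings of leaks and non-leaks are then equally likely. J fails to exceed 0 only if the ROC path never rises above the diagonal. When n1 and n0 share no common factor, that probability is exactly 1/(n1+n0).

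- 10/53: 1 − 1/63 = 0.984
- 11/59: 1 − 1/70 = 0.986
- 9/45 (common factor, so counted path by path): 0.978

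Averaging over a binomial number of leaks at 16% gives 0.981, 0.984 and 0.985 for N = 54, 63 and 70. If the direction is chosen after seeing the data, the figure is essentially 100%.

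**Step 3: what such a null cut-off looks like.** The median J is about 0.20 at 9/45 and 0.17 at 11/59. J exceeds 0.30 in 21% and 15% of null data sets respectively. At 10/53 the median apparent sensitivity and specificity are about 70% and 55%.

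**Step 4: the same data with the AUC test as a condition.** In simulation the lower 95% limit exceeding 0.50 was approximated by a one-sided Mann-Whitney test at 0.025. Under no association, a cut-off would be put forward in 2.3 to 2.8% of trials. At 10/53 the condition is passed in about 53% of trials at a true AUC of 0.70, 75% at 0.75 and 90 to 91% at 0.80.

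**The case against.** The strongest reply is that the protocol never says when its endpoint is met. Section 2.2 speaks of determining a cut-off, section 2.6.4 of hoping to, and section 2.7 gives an estimator, not a decision rule. This stands. The 98% is the frequency with which an estimator returns a positive value. A reader might infer a 98% false-positive rate, or a rule that always declares success, and the document supports neither.

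A reader might also infer that the study cannot give a negative answer. That goes too far. Section 2.4 plans around a significant AUC, and section 2.7 sets P < 0.05 and lists the Mann-Whitney test, which is equivalent to testing AUC = 0.50. A non-significant AUC would be a negative finding, and weak sensitivity and specificity would be visible to readers. But the AUC test is only implied: the Mann-Whitney test is to be used as needed, for no named purpose, and neither the endpoint nor the cut-off step refers to it.

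It can be said, too, that this is a condensed article and that a fuller protocol or SAP may add the link. It may. The point does not rest on missing detail, however. The article states the endpoint, the primary analysis and the sized hypothesis, and as stated they do not meet.

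Finally, this is early, single-centre observational work, and an AUC above 0.50 is a low bar that would not make a cut-off clinically useful. Both are true. The condition proposed below is a minimum for calling the cut-off predictive, not proof of usefulness.

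**Conclusion.** The concern holds as a disconnect between the primary endpoint and its analysis on one side (sections 2.2, 2.6.4 and 2.7) and the hypothesis behind the sample size on the other (section 2.4). The Youden step is unconditional and gives a better-than-chance cut-off in about 98% of data sets with no association, so the stated alpha and power do not carry over to a conclusion based on the cut-off.

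The 98% assumes a direction fixed in advance, a continuous marker and 9 to 11 leaks, and it describes the estimator, not an error rate. The null value of 0.50 is an assumption, since section 2.4 names none. The step should be corrected, though the gap is one of linkage: an AUC test is already implied.

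**What to change.** In sections 2.2 and 2.7:

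1. Make the primary analysis the AUC of one prespecified ICGA time for leakage, with a two-sided 95% CI, tested against 0.50. The time measure, the imaging moment and the direction need naming, because the article describes inflow and outflow times and two imaging moments, and the error rates in Step 4 hold for a single measure only. The interval method should be named too, since with about 10 leaks different methods need not agree.
2. Present the Youden cut-off as predictive only if the lower limit exceeds 0.50. Otherwise report that predictive ability was not shown, and label the cut-off descriptive.
3. In section 2.4, state the null AUC and the alternative AUC used for the 54.

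The cost is a few sentences, with no new data or patients. The price is that the primary result can be negative when ICGA does discriminate: with 63 patients, in about 25% of trials at a true AUC of 0.75 and about 10% at 0.80 (both AUCs assumed).

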### Ethics

2.8

This study will be conducted in accordance with the declaration of Helsinki and in agreement with the guidelines and principles of Good clinical practice. All patients will receive oral and written information before obtaining written consent in case of approval. This final version of the protocol was approved on 12/6/2018 by the medical ethical committee of Ghent University Hospital (EC/2018/0671), registered by the Belgian research committee (B670201836427), and submitted to the clinicaltrials.gov database (NCT03587532). Enrolment will start on September 1, 2018.

## Discussion

3

Esophageal anastomoses are fragile and prone to leakage, which is associated with significant morbidity, mortality, and impaired quality of life. The perfusion of the anastomosis is generally considered to be an important predictor for anastomotic integrity. During surgery the clinical judgment of the surgeon determines the anastomotic region based on subjective parameters. A good noninvasive method to objectively assess viability and both macro- and microvascular perfusion of the anastomotic site could help the surgeon to reliably decide the appropriate anastomotic region. Such a test needs to be easily available, cost effective, objective, and reproducible. NIRF imaging with ICG might combine all these advantages but is not yet calibrated nor validated. The proposed clinical study would be the first to use NIRF dynamic images to calculate physiologically relevant parameters (blood flow, blood volume, vascular leakage) and generate pseudocolor coded parametric maps using advanced curve analysis and compartmental modeling (AATH model).^[26,31]^ In addition, this study would be the first to validate imaging-based perfusion assessment of the stomach graft using tissue, serum, and cellular hallmarks of hypoperfusion and hypoxia. Data from this study will result in quantification of ICGA images, evaluate its potential to assess graft perfusion, and analyze its impact on AL after MIE for EC. The results of this project may allow to predict, and therefore avoid, AL after EC surgery. This may, in turn, prevent the morbidity and mortality associated with AL. Also, the results might contribute to a better understanding of gastric graft perfusion and oxygen supply in EC surgery.

In conclusion, this study will produce quantitative perfusion-related measurements for an objective ICGA assessment of tissue perfusion during surgery. The insights gained and the methods developed during this project may also benefit patients undergoing other types of cancer surgery (rectum, pancreas…) in which anastomotic tissue viability is of critical importance.
